### Phase II: economic analysis

#### Study design

A cost-efficiency analysis will determine the cost and potential economic net benefits of: (a) implementing the rapid index tests compared with comprehensive reference tests, and (b) conducting assessments in primary healthcare compared with specialist services.

#### Primary and secondary outcomes

Economic analyses will be secondary outcomes, which include: the (1) direct healthcare costs, and (2) indirect costs of diagnosing FASD using index tests compared with reference tests, (3) the direct healthcare costs and (4) indirect cost savings of delivering tests in primary healthcare compared with specialist clinics.

#### Participants

Two hundred families enrolled in Phase I will be asked about caregiver costs associated with index tests and reference tests. All sites will record health service costs associated with index tests and reference tests. Sites conducting comprehensive reference FASD assessments prior to the study will record health service costs of usual care for FASD assessments retrospectively.

#### Measures

##### Caregiver costs

Direct and indirect assessment costs for each family including clinical fees, childcare, accommodation and meals for assessment days will be surveyed from caregivers.

##### Health service costs

Prospective cost of delivering *index and reference tests* to participating children will be surveyed from practitioners and include: (1) discipline of the practitioner administering the test; (2) mode of delivery (e.g., clinic, home, school or telehealth); (3) travel time and costs; (4) test administration time; and (5) indirect administration time for the assessment (e.g., scoring and interpretation).

Usual cost of *reference tests* will be collected from clinical managers in a structured interview, including time taken to administer and score each measure, travel time and other costs.

#### Procedure

Prior to participant recruitment, the cost of index and reference tests (usual care) for health services will be retrospectively collected in a structured phone/video interview from site managers. Site manager responses will be recorded, transcribed and data will be extracted. Expected completion time for index and reference tests will also be extracted from test manuals. Families will be recruited and enrolled in the study as outlined in Phase I. Enrolled families and healthcare practitioners will complete surveys with one member from the research team that capture prospective cost information at the completion of testing. Therefore, the cost of index and reference tests will be collected retrospectively for tests administered as part of prior usual care from health service interviews, and costs will be collected prospectively for patients and health services recruited during the study period.

### Patient and public involvement

The rapid assessment used in the current project forms part of a tiered approach to screening, diagnosing and supporting FASD in remote Australian communities that was co-designed with First Nations Elders. Co-design involved First Nations Elders, a community advisory group, First Nations remote health practitioners, clinical experts and researchers. The research questions in the current project originated from a community advisory group because they asked, ‘What is necessary and sufficient to screen for and diagnose FASD?’ (ensuring judicious investment of resources), and ‘Who in the health care system is best placed to diagnose FASD in a remote setting?’ (reducing bottlenecks in specialist settings). Ongoing collaboration (focus groups, informal yarning, 3-monthly 1-week visits to community) between this group and the research team supported the development of the current protocol and this group has agreed to continue support for the duration of the project. Practitioners at new partner sites will be asked to identify a community representative interested in joining our advisory group. The advisory group will be informed of project progress and at the end of data collection, they will be involved in interpreting study results and will support dissemination of findings to local communities and the general public.

### Data analysis

#### Phase I: diagnostic accuracy

All data will be entered into an Research Electronic Data Capture (REDCap) database hosted by Griffith University.^19^ Data will be identifiable until all test results and survey data are matched to participants. Data will be de-identified for analysis. Prespecified test positivity cut-offs reflecting clinical norms (e.g., T score>70) will be used, receiver operating curves will also be used to explore best possible cut-offs. Standard diagnostic statistics will be calculated, including: receiver operating curves, sensitivity, specificity, positive and negative predictive values and likelihood ratios (using 95% confidence intervals).^20^ Kappa statistics will be used to compare the reliability of the classification of children as normal/moderately impaired versus severe on each measure of the neurodevelopmental domains.^21^ Continuous scores are available for many of the assessments, which will be used to calculate correlations between matched scores from the index tests and reference tests. Bland-Altman plots will examine the agreement between matched index test and reference test scores, overall and by domain.^21^ These plots will also help to determine if any difference between the index and the reference is influenced by the actual scores on the tests (e.g., if the index-standard difference is larger when children have low or high scores). Diagnostic outcomes from the index tests will be compared with diagnostic outcomes from the reference tests to explore whether the index tests function as an effective screening tool for FASD.

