#### Sample size

Sites conduct between 1-4 neurodevelopmental assessments per month as part of usual care. The number of FASD diagnoses completed at sites in the previous year was used to project a total recruitment sample of 288 children over 3 years of data collection. Allowing for 30% attrition, a final sample of 200 participants with 50% representation from rural and remote sites and 50% representation of First Nations children will be possible.

The probability of FASD diagnosis in this sample will be moderate (estimated at 50–60% across sites) because children are referred to sites due to significant developmental delays and suspected prenatal alcohol exposure. Two hundred participants provide a large enough sample for precise estimates of sensitivity and specificity. For example, assuming 55% of the sample have FASD, and the true sensitivity and specificity is 80% and 90%, respectively, we will be able to estimate sensitivity to within ±7.5% and specificity to within ±6.2% (alpha=0.05).

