Instructions can be non-verbal (shown not spoken), important for culturally diverse populations and children with English as a second language	

*The Rapid Neurodevelopmental Assessment (RNDA*) is a 30-minute observational and functional assessment identifying neurodevelopmental impairment in children from birth to 16 years. As well as screening for vision and hearing problems (that can affect task performance), it assesses motor (gross and fine), language, cognition, memory, attention, behaviour, and self-care. A series of age-appropriate structured tasks delivered by trained administrators follow specified decision rules detailed in the administration and scoring manual.^13^ As a functional assessment (rather than a normed assessment), children are given prompts and modelling to complete tasks if needed. Degree of impairment is classified as: typical, mild, moderate or severe impairment. Research demonstrates that the RNDA has sound to excellent inter-rater reliability across the neurodevelopmental domains with infant, child and adolescent populations.^14–16^ The RNDA has been reviewed by First Nations health practitioners and administered with First Nations children.^17^
*The Behavioural Assessment Scale for Children, Third Edition* is a 20-minute parent- and teacher-report of 2- to 21- year-old behavioural, emotional and social skills, as well as adaptive, attention and executive functioning in home, school and community settings.^18^ Both parent-report and teacher-report forms have excellent internal validity, very good test–retest reliability and inter-rater reliability.^18^

*Reference tests* were determined over a 6-month cross-site consultation process. Agreement on reliable and valid measures for nine domains was achieved in six steps (see table 2).

**Table 2 T2:** Steps to establish cross-site agreement for reference tests

Step	Activity
1	An international survey of clinical practice broadly ascertained the standard assessment protocol for each domain at neurodevelopmental assessment clinics globally.
2	A systematic review outlined the standard assessment protocol for each domain when detecting impairment for a fetal alcohol spectrum disorder diagnosis in internationally published research.^30^
3	Identification of tools from Step 1 and 2 with established Australian norms.

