4	A presentation to lead practitioners at each site introducing outcomes of Steps 1, 2 and 3. Lead practitioners took information to their clinical team to compare with site specific assessment protocols for each domain.
5	Monthly group meetings with lead practitioners across sites discussed pros and cons of preferred reference tests, until consensus was achieved.
6	When consensus could not be achieved on domain tests, the underlying construct of the domain was defined and consensus was achieved on subtests measuring similar constructs. For example, for academic achievement, a valid and reliable reading subtest exists in both the Wide Range Achievement Test^31^ and the Wechsler Individual Achievement Test.^32^

Table 3 outlines how the index tests correspond to reference tests selected for each neurodevelopmental domain used to diagnose FASD (excluding brain structure). All reference tests align with recommendations from the Australian guide to the diagnosis of FASD.^5^

**Table 3 T3:** Index and reference tests used to assess neurodevelopmental domains

Domain	Index test	Reference test
Motor	RNDA: Gross Motor and Fine Motor subscale	M-ABC 2 or BOT-2
Cognition	RNDA: Cognition subscale	WISC-V
Language	RNDA: Language subscale; BASC-3: Functional Communication scale	CELF-5*
Academic achievement	BASC-3: Learning Problems scale	WIAT-III or WRAT-5 or WJ-IV
Memory	RNDA: Memory subscale	CMS: Stories and Dot Location subscales
Attention	RNDA: Behaviour subscale (attention items); BASC-3: Attention Problems clinical scale	Connors-3 or Conners-4
Executive function	BASC-3: Executive Functioning index score	BRIEF-2
Affect regulation	RNDA: Behaviour subscale (affective items); BASC-3: Anxiety and Depression clinical Scale	Previous diagnostic status (depression/anxiety)
Adaptive behaviour, social skills Social communication	RNDA: Self Care subscale; RNDA: Behaviour subscale (peer play item); BASC-3: Adaptive Skills composite	ABAS-3 or Vineland-3

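### Accuracy quoted at the exploratory ROC-derived cut-offs would be somewhat optimistic, because the same roughly 200 children choose and test them and no correction is stated; accuracy at the prespecified cut-offs is not affected

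*Protocol article*

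**What the plan says.** The Phase I part of the data analysis section makes two statements about cut-offs in one sentence. Test positivity will follow cut-offs fixed in advance from clinical norms, and "receiver operating curves will also be used to explore best possible cut-offs". The next sentence lists sensitivity, specificity, predictive values and likelihood ratios with 95% confidence intervals. It does not say which set of cut-offs they belong to.

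The article describes one cohort and no separate validation sample. The sample size section states: "Two hundred participants provide a large enough sample for precise estimates of sensitivity and specificity". Its worked example, "assuming 55% of the sample have FASD, and the true sensitivity and specificity is 80% and 90%, respectively", leads to "we will be able to estimate sensitivity to within ±7.5% and specificity to within ±6.2% (alpha=0.05").

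Table 3 lists more than one index component for some domains. Language, for example, has "RNDA: Language subscale; BASC-3: Functional Communication scale". Attention has two components, affect regulation two (three if anxiety and depression are counted apart) and the adaptive/social domain three. The measures section describes the BASC-3 as a "20-minute parent- and teacher-report". The article gives no rule for combining these components, and does not say that one will be chosen over another. The RNDA grades impairment in four ordered categories.

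**The concern.** A cut-off that maximises accuracy in a sample is fitted partly to that sample's noise. Its apparent sensitivity and specificity in the same children are therefore higher, on average, than it would achieve in new children. A standard binomial interval treats the cut-off as fixed, so it is centred too high and takes no account of the search.

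The article's stated aim is for non-specialists to use rapid assessments in screening and diagnosis. If a ROC-derived cut-off is published with uncorrected accuracy, readers may take that accuracy as what they would see in practice. The precision in the sample size section also assumes a fixed cut-off, so it does not carry over to a searched one.

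**Working it through.** **1. The plan's own precision.** Inputs from the sample size section: 200 children, 55% with FASD, sensitivity 80%, specificity 90%, alpha 0.05.

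- With FASD: 200 × 0.55 = 110. Without: 200 − 110 = 90.
- Sensitivity half-width: 1.96 × √(0.8 × 0.2 / 110) = 7.5%.
- Specificity half-width: 1.96 × √(0.9 × 0.1 / 90) = 6.2%.
- Attrition: 288 × 0.70 = 201.6, consistent with a final 200.

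The stated figures reproduce for a cut-off fixed in advance.

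**2. Optimism from searching for the cut-off.** The following are assumptions, because the article does not give them: normal scores with equal variance, N(0,1) without and N(d,1) with the condition; *best* taken to mean the cut-off c* that maximises apparent sensitivity + specificity; the AUC; and domain prevalence (the article gives only FASD, "estimated at 50–60% across sites").

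- AUC = Φ(d/√2), so d = 2.12, 1.5 and 1.0 give 0.93, 0.86 and 0.76. The value 2.12 = 0.84 + 1.28 is the curve that passes through 80%/90%.
- True values at c*: sensitivity 1 − Φ(c* − d), specificity Φ(c*).
- Optimism = apparent (sensitivity + specificity) − true (sensitivity + specificity), averaged over 1,500 simulated samples of 200.

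Mean optimism in points, sensitivity and specificity summed, continuous scores (competing scores correlated 0.5):

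| Prevalence (with/without) | AUC | One score | Best of two | Best of three |
|---|---|---|---|---|
| 55% (110/90) | 0.93 | 4.4 | 6.2 | 7.1 |
| 55% (110/90) | 0.86 | 4.8 | 7.1 | 8.5 |
| 55% (110/90) | 0.76 | 6.0 | 8.1 | 9.3 |
| 30% (60/140) | 0.93 | 4.3 | 6.4 | 7.6 |
| 30% (60/140) | 0.86 | 5.4 | 7.7 | 9.1 |
| 30% (60/140) | 0.76 | 6.1 | 8.7 | 10.2 |
| 20% (40/160) | 0.93 | 5.2 | 7.7 | 8.8 |
| 20% (40/160) | 0.86 | 6.6 | 9.0 | 10.9 |
| 20% (40/160) | 0.76 | 7.3 | 10.4 | 11.7 |

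With independent scores at AUC 0.85 and 40/160, the best of three gives 11.6 to 12.0 across repeated simulations. At 10% prevalence, outside the range used here, one score gives 7.6 to 10.9.

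**3. Four-category scores, as the RNDA yields.** Only three cut-offs are possible, so there is little to search. At 20% to 55% prevalence:

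- One score: 0.1 to 0.6 at AUC 0.93, and 1.3 to 2.6 at AUC 0.76.
- Better of two: 2.5 to 3.3 at AUC 0.93, and 3.6 to 5.4 at AUC 0.76.

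**4. Each measure separately, one continuous score.** At 55% prevalence and AUC 0.93, the 4.4 points split into about 2.0 for sensitivity and 2.4 for specificity. Against the planned half-widths these are 2.0/7.5 = 0.27 and 2.4/6.2 = 0.39. At 20% prevalence and AUC 0.86, the 6.6 points split into 5.4 and 1.2. Sensitivity then rests on 40 children, with a half-width at 80% of 1.96 × √(0.16/40) = 12.4%, so the ratio is 5.4/12.4 = 0.44.

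**5. Intervals.** In simulations of continuous scores, nominal 95% Wilson intervals at the selected cut-off covered the true sensitivity 91% to 94% of the time with one score. Coverage was 85% to 92% for the best of two and 80% to 89% for the best of three.

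**The case against.** The strongest reply is that the plan already puts prespecified cut-offs first, and its wording makes the ROC search additional and exploratory. That stands: nothing here touches accuracy at the prespecified cut-offs. A reader might infer that the trial's main accuracy results are inflated, but the article does not support that.

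A second reply is that this is a condensed article whose analysis plan is not shown, and optimism correction is the kind of detail such a plan may hold. This stands in part. The point is therefore not that a correction is missing from every document. The analysis as written, a search followed by standard statistics and intervals in one cohort, gives optimistic figures if it is followed literally.

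A third reply concerns Table 3. A reader might infer that the listed scores, or the parent and teacher BASC-3 forms, compete and that the best performer will be reported. The article says no such thing. The components may be meant to be combined, and some cover different facets of a domain. The best-of-two and best-of-three figures are therefore conditional.

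Finally, no continuous FASD score is described. FASD is defined as three severe domains plus prenatal alcohol exposure. The 110/90 rows therefore illustrate the effect at the planning prevalence and do not model the diagnosis itself. This also stands.

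**Conclusion.** The point holds for accuracy quoted at ROC-derived cut-offs, and only there. On the assumptions above (AUC about 0.85 to 0.93, prevalence 20% to 55%, cut-off maximising the sum), one continuous score gives about 4 to 7 points of optimism in sensitivity plus specificity taken together. Four-category RNDA scores give about 0 to 5, and the upper end needs both a lower AUC (0.76) and a choice between two scores. For one continuous score, the bias in either measure alone is smaller than its interval half-width, at roughly a quarter to under a half of it in the cases worked.

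A flat statement that accuracy will be overstated by 5 to 12 points is tempting but not supported. At the plan's own values one continuous score gives 4.4, the RNDA categories mostly give less than 5, and figures near 12 require a best-of-several selection that the article does not describe. The matter deserves correction because the remedy is cheap and the bias runs in a known direction, but it does not threaten the prespecified analysis.

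**What to change.** State that headline sensitivity and specificity come only from the prespecified cut-offs. Label ROC-derived cut-offs exploratory, name the criterion for the best cut-off, and report them in a separate table.

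For that table, give optimism-corrected values. Resample children with replacement and repeat the cut-off choice in every resample, together with the choice of score if one is made. Subtract the average difference between accuracy in the resample and accuracy of the same rule in the original sample. Take the intervals from a bootstrap that also repeats the selection. For domains with several index components, fix before analysis how they are combined or which one counts, so that no selection among scores arises.

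The cost is a little code and a few sentences, with no new data. The exploratory figures will come out a few points less favourable.

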#### Phase II: economic analysis

A multivariable generalised linear model of the cost of diagnosis, with the predictive variable as the index test or reference test, will estimate the incremental cost between the two alternative diagnostic processes adjusting for differences in patient geographical location and other potential confounders. Subgroup cost analysis will explore heterogeneity of results between patients’ subgroups by including an interaction term (e.g., location, diagnostic procedure) within the multivariable generalised linear model of cost. The expected value of implementation will be calculated as the net monetary benefit of the index tests (i.e., monetary benefits — costs) multiplied by the population of patients expected to benefit from the reference tests. Probabilistic and one-way sensitivity analysis will be used to characterise the uncertainty in the economic results, highlighting the most important drivers for the value of implementing the index tests.

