**Trial registration number:**

ACTRN12622000498796.

Strengths and limitations of this studyDATAforFASD is the first large, prospective, multi-site trial to compare comprehensive assessments to rapid assessments across nine domains of neurodevelopment so that we can better understand the accuracy of using rapid assessments to screen and diagnose neurodevelopmental disorders like fetal alcohol spectrum disorder (FASD).A sample size of at least 200 children is uncommon in FASD research and may prove to be challenging, because completing gold-standard comprehensive assessments on nine neurodevelopmental domains requires around 2 days of multidisciplinary specialist (paediatrician/allied health) time per child.The rapid assessment fits within a co-designed tiered assessment process that is responsive to cultural protocols and limited healthcare resources in remote regions. It includes the Rapid Neurodevelopmental Assessment, an observational functional neurodevelopmental assessment and the Behavioural Assessment Scale for Children, Third Edition.This project follows standards for reporting diagnostic accuracy study (STARD) guidelines, providing the methodological rigour necessary to assess the diagnostic accuracy of rapid assessments in identifying FASD, as well as their accuracy in identifying neurodevelopmental impairment across nine domains; the cost benefit of using rapid assessment will be explored for families and health services.Establishing valid, accurate rapid assessments will enable: (a) early detection of at-risk children, particularly in rural and remote communities where access to care is inequitable; (b) non-specialist care providers (health, education, youth justice, child protection) to confidently contribute to information needed for diagnostic purposes; (c) enhanced triage, resulting in better quality referrals to specialists; (d) the use of rapid assessments for diagnostic purposes, potentially addressing a systemic healthcare challenge by offsetting the longest most costly assessment process for the most prevalent preventable neurodevelopmental disorder.

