## Introduction

Fetal alcohol spectrum disorder (FASD) affects between 1 - 5% of Australian children, and up to 19% in some remote Australian communities, which is higher than any other neurodevelopmental disorder.^1–4^ To identify FASD, current Australian guidelines recommend comprehensive diagnostic assessments (reference tests) across 10 neurodevelopmental domains, delivered by multidisciplinary teams. These assessments are primarily available in Australia at specialist services, making this a lengthier and more costly diagnostic process than any other neurodevelopmental disorder.^5^ Current waitlists for Australian children suspected of FASD are up to 3 years at some health services. Overall, specialist services are only seeing a small proportion of suspected cases and children from rural and remote regions are left behind.^6 7^

To meet the demand for diagnosis, our Australian health system either needs an inordinate number of specialists and multidisciplinary clinics, or we need to think differently about how to diagnose FASD. Our health system is unlikely to be able to resource the longest, most costly assessment process for one of the most prevalent neurodevelopmental disorders in children, but the use of valid and reliable rapid assessment tools could leverage capacity within primary care, increasing vulnerable children’s access to diagnosis.

In this project we will conduct a two-phase study to: (1) determine the diagnostic accuracy of rapid neurodevelopment assessments (index tests) that can be used to detect FASD in primary healthcare (Phase I)^8^; and (2) examine the economic benefits of leveraging primary healthcare to support specialist practitioners in the diagnosis of FASD, in terms of cost for families and healthcare systems (Phase II).

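### The Phase II cost model fixes only a replacement contrast, so it would overstate the saving for the tiered or triage use that the protocol also intends

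*Protocol article*

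**What the plan says.** The Phase II analysis regresses cost on which of the two test sets was used. According to the article, this model "will estimate the incremental cost between the two alternative diagnostic processes". The contrast agrees with the Phase II study design, whose first comparison is "implementing the rapid index tests compared with comprehensive reference tests", and with the Phase II outcomes, which list direct and indirect costs of diagnosis by one test set against the other. A second comparison sets delivery in primary healthcare against delivery in specialist services. No strategy is named in which a child has the index tests and then, depending on the result, the reference tests.

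On intended use the article is mixed.

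- **Alongside specialists.** The Introduction gives the Phase II aim as to "examine the economic benefits of leveraging primary healthcare to support specialist practitioners in the diagnosis of FASD". The strengths and limitations list includes "enhanced triage, resulting in better quality referrals to specialists". The Phase I analysis compares diagnostic outcomes "to explore whether the index tests function as an effective screening tool for FASD". The Abstract places the index tests within a tiered process, and the Summary wants practitioners to know when to diagnose and when to involve a specialist.
- **In place of the comprehensive assessment.** Item (d) of the strengths list foresees diagnostic use that offsets the long and costly assessment. The first primary outcome is accuracy in identifying FASD, and the Summary speaks of diagnosis within primary healthcare.

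**The concern.** In tiered use, the cost per child is the index cost plus, for each child sent on, the reference cost. A contrast of two alternatives cannot give that sum. Every participant completes both test sets for validation, so nobody in the study follows the tiered pathway and its cost has to be constructed. The analysis as written does not construct it.

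A replacement saving could then be quoted as the benefit of triage or of support to specialists, and the error would favour the index tests. If the same incremental cost feeds the planned net monetary benefit, multiplying by a patient population carries the error into the expected value of implementation.

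**Working it through.** **The plan's own figures.** The article states no cost saving, so there is none to reproduce. Its planning values come from the Sample size section, "assuming 55% of the sample have FASD, and the true sensitivity and specificity is 80% and 90%, respectively", and the precision quoted there does reproduce. With 200 children, 110 have FASD and 90 do not:

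- Sensitivity: 1.96 × √(0.80 × 0.20 / 110) = 7.5%
- Specificity: 1.96 × √(0.90 × 0.10 / 90) = 6.2%

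**Inputs for the illustration**

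- Index time: 30 minutes (RNDA) + 20 minutes (BASC-3) = 50 minutes = 0.83 h, from Measures.
- Reference time: about 2 days of specialist time, from the strengths and limitations list. Taking this as 12 to 16 h is my assumption.
- Time stands in for cost, because the article gives no unit costs.

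**Share index-positive**

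q = 0.55 × 0.80 + 0.45 × 0.10 = 0.440 + 0.045 = 0.485

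**Saving per child against reference tests for all.** Let R be the reference time, I the index time, and k the proportion of index-positive children referred on to the full reference tests.

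- Replacement: R − I
- Tiered: R × (1 − kq) − I
- Overstatement factor: (R − I) / [R × (1 − kq) − I]

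For example, with R = 16 and k = 1, the tiered saving is 16 × 0.515 − 0.83 = 7.41 h. The replacement saving is 16 − 0.83 = 15.17 h, and the ratio is 2.05.

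| k | Share referred (kq) | Saving, R = 16 h | Factor | Saving, R = 12 h | Factor |
|---|---|---|---|---|---|
| 0 (replacement) | 0 | 15.17 h | 1.00 | 11.17 h | 1.00 |
| 0.5 | 0.2425 | 11.29 h | 1.34 | 8.26 h | 1.35 |
| 1 | 0.485 | 7.41 h | 2.05 | 5.35 h | 2.09 |

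**Sensitivity of the k = 1 result**

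- Prevalence of 50% to 60%, the range in the Sample size section: q = 0.45 to 0.52, factor 1.90 to 2.22 (R = 16 h).
- Index cost as a fraction r of reference cost, using (1 − r) / (0.515 − r): 2.17 at r = 0.10 and 2.54 at r = 0.20. The factor grows if the index tests are dearer than the 50 minutes suggest.
- Sensitivity and specificity each between 0.7 and 0.9, at r = 0.05: factor 1.8 to 3.0.

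**Missed cases.** Index-negative children with FASD are 0.55 × 0.20 = 0.11 of the sample, or 22 of 200. A tiered cost that only subtracts their reference tests would count these misses as saving.

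**The case against.** The strongest reply is that the model matches its stated objective. Design, outcomes and analysis all say index against reference, and for diagnostic use that is the right contrast. This stands, and it is why the planned contrast should be kept.

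A reader might infer that the index tests are meant only as a triage tier, that every index-positive child must go on to the reference tests, and that the plan therefore overstates the saving two-fold. The article does not support this. It foresees diagnostic use as well, nowhere requires reference tests for all index-positive children, and in the Summary leaves room for diagnosis without a specialist. It also claims no saving. The accuracy values are an example chosen to show precision. The 50 minutes leave out scoring, interpretation and travel, all of which the study will cost.

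Two further objections carry less weight. The comparison of primary healthcare with specialist delivery bears on the Phase II aim, but it concerns where tests are delivered and does not supply the cost of a child who has both test sets. A fuller economic plan may also contain pathway scenarios, and net monetary benefit and sensitivity analyses are already foreseen. But the contrast is a choice the article states, not a detail it leaves open, and the care pathway is not named among the drivers to be varied.

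**Conclusion.** The point holds in a limited form. The planned contrast is correct for replacement. For the tiered, triage or specialist-supporting use that the protocol also names, it overstates the saving as soon as any child is referred on.

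The direction does not depend on the illustrative values; the size does. The factor is 1.0 with no onward referral, about 1.3 if half of index-positive children are referred, and 2.0 to 2.1 if all are. These figures rest on the planning prevalence and accuracy, on time as a proxy for cost, on 2 days being 12 to 16 h, and on referred children having the full reference tests. A shortened battery after referral would lower the factor. The economic analyses are secondary outcomes, so the primary accuracy results are not affected.

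**What to change.** In the Phase II economic analysis:

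1. Keep the index-versus-reference contrast and label it as the replacement comparison.
2. Add a second named strategy: index tests for all, reference tests for children referred on. Compute it per child from the recorded index cost, reference cost and index result, and compare it with reference tests for all.
3. Vary the referral proportion in the one-way sensitivity analysis already planned.
4. Report the number of index-negative children with FASD beside the tiered cost, so that missed cases are not read as pure saving.
5. Rest any statement about screening, triage or support to specialists on the tiered contrast.

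The cost is a change of wording and a little more analysis. Caregiver and practitioner costs for both test sets are already to be collected, and Phase I supplies the index result. The reported saving for the tiered use will be less favourable.
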